		**Effect size**		
**Risk behaviours**	**Control**[7]	**ICC = 0.01**	**ICC = 0.04**	**ICC = 0.07**
Alcohol use	41%	11%	13%	15%
Substance abuse	38%	11%	13%	15%
Tobacco use	24%	9%	10%	12%

ICC = Intracluster Correlation Coefficient; Control = comparison arm.

*Calculations assume an 80% power with alpha of 5% for a two-sided test.

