#### ***Sample size estimation***

Sample size calculations assumed 80% power at a significance level of 5% for two- sided test and an intra-clinic correlation of 0.04 [63]. The original first hypothesis was based on the assumption that 40% of youth attending general practice have health risk behaviours or emotional distress, and that trained GPs, at best, will pick up 60% with interview alone [17], equivalent to 24% of all presenting youth. For a clinically meaningful outcome, we expected the clinicians to detect a further 25% of youth with risk taking behaviours using the screening tool with the interview (intervention arm), equivalent to an additional 10% of all presenting youth to the practice, compared to the comparison arm. To detect a 10% difference in the clinician’s detection of risk taking behaviours of all youth attending general practice between the two study arms, 1760 youth (44 per practice in 40 practices) were required after allowing for a variance inflation factor (VIF) of 2.72.

To allow for the slow recruitment rates, we revised our intended intervention effect in the clinician’s detection of risk taking behaviours of all youth attending general practice from 10% to 12.5% (equivalent to intervention clinicians picking up a further 31% of youth with risk taking behaviours instead of the 25% originally proposed). This small adjustment to the effect size reduced the required sample size to a total of 720 youth (18 per practice in 40 practices with a VIF of 1.68). To allow for a 40% loss to follow-up of youth over 12 months [64], we calculated that a total of 30 youth in each practice needed to be interviewed at recruitment. An additional two practices were also recruited to allow for loss of practices during follow-up.

The revised sample size also affects the difference in the prevalence of the risk behaviours that can be detected between the study arms in the second hypothesis. Table 2 gives the minimal effect size that can be detected in the prevalence of selected risk behaviours between the study arms at 3 and 12 months follow-up (power 80%, alpha 5% for a two-sided test) for the revised sample size for a range of intra-cluster correlations. The revised sample size is sufficient to detect at least a 15% difference between the two study arms for each of the risk behaviours with 80% power and alpha at 5% for a two-sided test.

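### Table 2 prints 10% as the detectable tobacco effect at the planning ICC of 0.04, but that effect has about 75% power, not the stated 80%; the entry should be 11%

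*Protocol article*

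**What the plan says.** The section Sample size estimation assumes 80% power with a "two- sided test and an intra-clinic correlation of 0.04". The revised requirement is "a total of 720 youth (18 per practice in 40 practices with a VIF of 1.68"). The allowance for attrition ("To allow for a 40% loss to follow-up of youth over 12 months") raises recruitment to 30 per practice, which leaves 18 per practice for analysis.

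The same section then says that "Table 2 gives the minimal effect size that can be detected in the prevalence of selected risk behaviours" between the arms at 3 and 12 months, "for the revised sample size for a range of intra-cluster correlations". The note under the table repeats the power and significance level: "Calculations assume an 80% power with alpha of 5% for a two-sided test".

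The tobacco row gives a comparison-arm prevalence of 24% and detectable effects of 9%, 10% and 12% at ICCs of 0.01, 0.04 and 0.07. Alcohol use (41%) and substance abuse (38%) each have 11%, 13% and 15%.

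**The concern.** The middle tobacco entry looks too small beside its neighbours. All nine cells should come from one formula with the same sample, power and significance level. Eight of them do, if each result is rounded up to a whole percentage point. The tobacco entry at ICC 0.04 lies below its computed value, so the design does not have the stated power at the stated effect. It stands in the ICC column that was used to set the sample size, and a reader judging a null tobacco result would take 10 points as the difference the trial had 80% power to find.

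**Working it through.** **Inputs.** From Sample size estimation: two-sided alpha 5%, power 80%, 720 youth as 18 in each of 40 practices. From Table 2: comparison-arm prevalences and effects. Two readings are inferred. Arms are equal, 360 youth each, because randomisation used fixed blocks of two. Effects are reductions, the direction of the second hypothesis under Study questions.

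**Formula.** Design effect = 1 + (18 − 1) × ICC. Effective number per arm = 360 / (1 + 17 × ICC). Power is the usual normal approximation for two proportions with pooled variance under the null; the detectable difference is the value that gives 80%.

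**Check on the article's own totals.**
- 24% against 34%: 323 per arm before clustering; 323 × 2 × 2.72 = 1757 (article: 1760).
- 24% against 36.5%: 211 per arm; 211 × 2 × 1.68 = 709; 709 / 40 = 17.7, so 18 per practice and 720 in all (article: 720).

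The formula reproduces both planned sample sizes.

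**The tobacco cell at ICC 0.04.**
- Effective number per arm = 360 / 1.68 = 214.3.
- Standard error for 24% against 14% = √[(0.24 × 0.76 + 0.14 × 0.86) / 214.3] = 0.0376.
- Unpooled power = Φ(0.10 / 0.0376 − 1.96) = Φ(0.70) = 75.8%.
- With the pooled null standard error, √(2 × 0.19 × 0.81 / 214.3) = 0.0379: power = Φ[(0.10 − 1.96 × 0.0379) / 0.0376] = 75.3%.
- Difference needed for 80%: 10.53 points pooled, 10.47 unpooled.

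**All nine cells (pooled variance).**

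| Behaviour | ICC | Printed | Computed | Power at printed value |
|---|---|---|---|---|
| Alcohol | 0.01 | 11 | 10.79 | 81.5% |
| Alcohol | 0.04 | 13 | 12.84 | 81.0% |
| Alcohol | 0.07 | 15 | 14.56 | 82.5% |
| Substance | 0.01 | 11 | 10.58 | 83.1% |
| Substance | 0.04 | 13 | 12.56 | 82.8% |
| Substance | 0.07 | 15 | 14.23 | 84.3% |
| Tobacco | 0.01 | 9 | 8.94 | 80.6% |
| **Tobacco** | **0.04** | **10** | **10.53** | **75.3%** |
| Tobacco | 0.07 | 12 | 11.85 | 81.1% |

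Eight entries are the computed value rounded up. The ninth is rounded down.

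**Other formulas for the same cell, 720 youth.** Power at 10 points is 75.8% with the arcsine approximation, 74.3% on the log odds ratio scale, 73.6% with a t reference on 38 degrees of freedom, 71.2% with a continuity correction and 67.9% with the comparison-arm variance used for both arms. With all 42 practices (756 youth) it is 77.3%. None reaches 80%.

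**After the change.** At 11 points power is 83.7% pooled and 84.2% unpooled. It is 80.4% with the continuity correction. Only the comparison-arm-variance formula stays below 80% (76.0%). That formula is not the source of the table either, since it gives 9.65, 11.56 and 13.20 for the tobacco row.

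**The case against.** The best counter-argument is that this is rounding. With the arcsine approximation and rounding to the nearest point, tobacco at ICC 0.04 is 10.47, which prints as 10, and eight of the nine entries match. The misfit then moves to substance abuse at ICC 0.07, computed as 14.19 and printed as 15. On that reading the odd cell is a different one and errs on the cautious side. The prevalences are also printed as whole percents: a true 23.5% would give 10.43 points, which rounds to 10. Finally, 720 was set by the clinician-detection outcome, not by Table 2, so no sample size or hypothesis depends on this cell.

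Part of this stands. How the slip arose cannot be known, and its consequence is small. But no single convention examined reproduces all nine entries, and nearest rounding does not repair the claim. Whatever rule produced the 10, the note promises 80% power at the printed effect, and 10 points gives 75-76% (76-77% even at 23.5%). Substance abuse printed as 15 keeps the promise; tobacco printed as 10 does not. The continuity-corrected calculation with nearest rounding also reproduces the other eight entries, and it gives 10.95, so 11, for this cell.

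Nor does a larger sample at 3 months explain the entry. With no attrition (1200 youth) 10 points would have 85.4% power, but the text ties the table to the revised sample size, and the other entries would then be far too large.

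**Conclusion.** The concern holds. At the article's planning ICC of 0.04 and its 720 youth, a tobacco reduction from 24% to 14% has about 75% power, roughly 5 points below the stated 80%. The smallest reduction detectable with 80% power is 10.5 points. Reaching 80% for the printed 10 points would take about 808 youth by the same formula (240.4 × 2 × 1.68).

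This rests on equal arms, 18 analysed youth per practice and effects read as reductions. That it is the only deficient cell also depends on the formula: it is true with pooled, unpooled or arcsine variance. With a continuity correction or a t reference some other entries also dip slightly below 80%, but this cell remains the lowest. Read as increases, all nine entries fall below 80%, and this one has 62.7%.

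The importance is minor. The article's statement that at least a 15% difference is detectable for each behaviour still holds, and the design, conduct and analysis are untouched.

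**What to change.** In Table 2, change the tobacco entry at ICC 0.04 from 10% to 11% (or print 10.5%). Add to the table note that effects are reductions from the comparison-arm prevalence, computed for 18 youth in each of 20 practices per arm, and rounded up to whole points; name the formula there. The cost is one cell and one sentence, and the stated figure becomes slightly less favourable. Nothing else in the article has to change.

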#### ***Measures developed***

Outcome measures were developed for baseline, post-intervention and follow-up at three and 12 months. Data were collected from five sources: the practice, practice staff, young people and parents (if accompanying the young person) and the clinicians’ reports of the consultation in the clinical encounter form. The measures used to collect the data are detailed in Table 1. Phase of administration refers to phase of the trial flow detailed in Figure 2.

### **Data analysis plan**

Quantitative outcomes: Descriptive statistics will be used to compare clinician and young person’s characteristics between the two study arms at baseline and measures taken immediately after the consultation. Intra-cluster correlation will be reported for the main outcomes. Analysis will be by intention to treat and results will be reported following the extended consort statement for cluster randomised trials [58]. Marginal linear and logistic regression models using generalised estimating equations with robust standard errors will be used to adjust for the clustering effect of randomising the general practices and outcomes measured at the young person’s level. Marginal logistic regression will be used to estimate the intervention effect for binary outcomes and will be reported as odds ratios. Marginal linear regression will be used to estimate the intervention effect for continuous outcomes and will be reported as the difference in the mean outcome between the two study arms. Estimates of the intervention effect will be reported with their respective 95% confidence intervals and p-values. Multivariable regression models will be used to adjust for variables used to stratify randomisation (SES of the practice location, practice billing type) and for imbalanced baseline factors identified a priori to be strongly associated with the outcome, namely the baseline risk factor status of young people and prior training in adolescent health. Recruitment method of young people in the trial will also be adjusted for in the regression model (clinician versus research assistant).

Qualitative outcomes: Interviews with practice staff on acceptance of screening processes will be transcribed and analysed for themes. Secondary outcomes of pathways to care (health service use) [65] will be described and parental attitudes will be summarised for each arm.

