#### ***Post-intervention sampling of young people and parents***

Eight weeks after randomisation and six weeks after the practice staff completed the intervention, practices recruited the young patients who formed the cohort followed up at three months and 12 months post-consultation. Clinicians were again instructed to recruit all eligible young people aged 14–24 years with whom they consulted until the required sample size for each practice was achieved. Parents attending with young people under the age of 18 years were instructed to complete the written parent survey and return it to researchers in a reply paid envelope. Clinicians again completed a clinician encounter form on each youth consult.

Our monitoring of recruitment rates of young people revealed that clinicians were failing to recruit continuously, and systematically; the timeframe for recruitment extended over long periods that varied from 13 days to nearly 11 months (mean 86.3 days). Within the longer periods, recruitment was inconsistent, influenced by practice constraints (e.g., accreditation activities, staff absence including extended sick leave as was the case for the practice which took 11 months). To complete the study within a reasonable timeframe and to ensure that all eligible young people were approached and recruited into the study, we changed our recruitment strategy for the last 15 practices by placing a research assistant in the waiting room to systematically approach every young person with an invitation to be involved. Slightly more intervention practices (8/19 intervention versus 7/21 comparison practices) received this assistance because recruitment in the intervention practices was delayed after randomisation due to longer times taken for training clinicians compared to the comparison practices. The additional benefit of the in-practice research assistants was the timely, daily transfer of phone numbers of eligible young people to the CATI interviewers and accurate recording of reasons for refusal to participate or ineligibility.

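### With 40 practices and at least four practice-level covariate terms, the planned robust GEE tests run at about 7-10% instead of 5% unless a small-sample correction is applied

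*Protocol article*

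**What the plan says.** All references are to the Protocol article.

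- **Method** (Data analysis plan): "Marginal linear and logistic regression models using generalised estimating equations with robust standard errors will be used to adjust for the clustering effect". It covers continuous and binary outcomes, and effects are to be reported with 95% confidence intervals and p-values.
- **Covariates** (same section): "Multivariable regression models will be used to adjust for variables used to stratify randomisation (SES of the practice location, practice billing type", the latter having three categories under Randomisation. Recruitment method (clinician or research assistant) is also adjusted for. Baseline risk status and prior training in adolescent health enter among the imbalanced baseline factors.
- **Practices** (Post-intervention sampling of young people and parents): research assistants recruited in "8/19 intervention versus 7/21 comparison practices", so there are 40 clusters, 15 of them assisted.
- **Error level** (Sample size estimation): "Sample size calculations assumed 80% power at a significance level of 5% for two- sided test and an intra-clinic correlation of 0.04".

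No small-sample correction, degrees of freedom or reference distribution is mentioned. The article does not say that the standard errors are uncorrected either.

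**The concern.** The sandwich variance is justified when there are many independent clusters. Here there are 40, however many young people are interviewed. A covariate that is constant within a practice is estimated from those 40 units, and each such term makes the fitted residuals smaller than the true ones. The ordinary sandwich estimator is built from those residuals, so it is biased downward, and a normal reference ignores the uncertainty in the variance estimate. Both errors favour a positive result. At stake are the level of the tests and the coverage of the intervals for every outcome analysed with these models, including detection of risk and the risk behaviours at 3 and 12 months.

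**Working it through.** **1. The plan's own sample size.** The inputs are two-sided 5%, 80% power, ICC 0.04, and a comparison-arm detection rate of 24% ("at best, will pick up 60% with interview alone [17], equivalent to 24% of all presenting youth"). The variance inflation factor is 1 + (m − 1) × 0.04, and the number per arm comes from the pooled two-proportion formula without continuity correction.

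- Original, 24% v 34%, m = 44: 1 + 43 × 0.04 = 2.72. 323 per arm × 2 × 2.72 = 1757. The plan says "1760 youth (44 per practice in 40 practices) were required after allowing for a variance inflation factor (VIF) of 2.72".
- Revised, with the difference in "clinician’s detection of risk taking behaviours of all youth attending general practice from 10% to 12.5" percentage points, i.e. 24% v 36.5%, m = 18: 1 + 17 × 0.04 = 1.68. 211 per arm × 2 × 1.68 = 709. The plan says "a total of 720 youth (18 per practice in 40 practices with a VIF of 1.68".
- Loss to follow-up: 18 / (1 − 0.40) = 30 per practice.

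These figures reproduce. They use normal quantiles and make no allowance for the number of clusters.

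**2. Counting practice-level terms.** SES has two levels (1 term), practice type three (2 terms), and recruitment method 1 term, since it changed for the last 15 practices. That makes four unconditional terms. With the intercept and arm there are 6 parameters, leaving 40 − 6 = 34 degrees of freedom. Prior training and baseline risk may add two: 8 parameters, 32 degrees of freedom. The baseline sample was a different set of young people, so risk status from the baseline profile could enter only as a practice summary.

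**3. Type I error by simulation.** There was no intervention effect, and 40 practices were allocated in blocks of two within strata. Outcomes were beta-binomial, analysed by logistic GEE with exchangeable working correlation. Scenarios took ICC 0.01, 0.04 or 0.07, prevalence 24%, 34% or 41%, and mean cluster size 18, 24 or 30, equal or with a coefficient of variation of 0.4. Each had 3000-4000 replicates (Monte Carlo error about 0.4-0.5 points). Results for the ordinary sandwich with a normal reference:

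| Model | Parameters | SE too small by | Type I error |
|---|---|---|---|
| Arm only | 2 | about 4% | 5.9-6.6% |
| + SES, billing type | 5 | 7-10% | 6.7-8.7% |
| + recruitment method | 6 | 8-12% | 7.8-9.1% |
| + prior training, baseline risk (practice level) | 8 | 11-13% | 8.3-10.0% |

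Separate runs with only the four unconditional terms gave 8.0-8.4%, against 5.6-6.5% with arm alone. Another set (19 v 21, ICC 0.04, prior training added to those four terms) gave 7.7-8.9%, against 6.4-7.2%.

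**4. Analytic cross-check.** If the standard error is r times its true size, the level is 2 × [1 − Φ(1.96 r)]. This gives 6.0% for r = 0.96, 7.1% for 0.92, 7.8% for 0.90 and 8.8% for 0.87. The simulated levels lie at or somewhat above these, as expected when the standard error also varies from trial to trial. Coverage is one minus the level: about 93% at 6.7% and 90% at 10.0%.

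**5. Which corrections work in the adjusted models.**

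| Approach | Type I error |
|---|---|
| K/(K − 1) scaling, normal reference | 6.5-9.7% |
| Ordinary sandwich, t on K − p | 6.0-8.8% |
| Mancl-DeRouen, normal reference | 3.1-5.1% |
| Kauermann-Carroll, t on K − p | about 4.5-5.8% |

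**The case against.** The strongest counter-argument is that lack of correction is inferred from silence. A Kauermann-Carroll sandwich with a t reference is still a GEE with robust standard errors, so the remedy is compatible with the plan's sentence. The article condenses a fuller plan, and an analysis plan not shown may already fix the correction. This stands, and it is why the point is conditional. It does not dispose of the point: the article names the variance estimator, and in its ordinary form that estimator misses the stated 5% level in the adjusted models.

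A reader might also infer four stronger claims that the documents do not support.

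- **That the plan commits to uncorrected errors and a normal reference.** It states neither.
- **That every primary outcome is affected.** Acceptability is a primary aim, but staff acceptance is analysed by themes and parental attitudes are summarised by arm.
- **That five practice-level covariate terms are certain.** Prior training enters only if imbalanced, and Table 1 records it in the staff survey for each clinician, so it need not be practice-level. The four unconditional terms nevertheless give about 8-9%.
- **That 40 practices are in themselves too few.** With arm alone the level is about 6-7%.

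Finally, the choice of correction is partly a preference. Mancl-DeRouen also controls the level, at times conservatively.

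**Conclusion.** The concern holds in conditional form. Unless a small-sample correction is applied, standard errors in the adjusted models are about 7-13% too small, tests run at roughly 7-10% instead of 5%, and nominal 95% intervals cover about 90-93%. The excess is moderate. It appeared in every adjusted scenario tried and comes mainly from the practice-level covariates. It applies to the outcomes tested with the GEE regressions.

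The size rests on assumptions the article does not settle: the stratum shares, the share with prior training, the cluster-size variation, the exchangeable working correlation, and practice-level entry of the two conditional covariates. Removing those two leaves 7.8-9.1%. Severity: it should be addressed, and it does not undermine the design.

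**What to change.** Keep GEE and the planned covariates. State, for all GEE tests and confidence intervals, a small-sample corrected sandwich variance (for example Kauermann-Carroll) with a t reference on practices minus practice-level parameters. If the full analysis plan already does this, saying so closes the point. The article's Discussion says that analysis is under way, so the choice should be documented as independent of the results.

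The change takes one sentence and a software option. Its real cost is width. Removing the standard error bias and replacing 1.96 by the t quantile multiplies the interval by (1/0.92) × (2.032/1.960) = 1.13 with 34 degrees of freedom and a ratio of 0.92. With 32 degrees of freedom and a ratio of 0.87 it is (1/0.87) × (2.037/1.960) = 1.19. Adjusted intervals are therefore roughly 13-19% wider.

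The t quantile itself costs little power. At N = 720, each arm has 360/1.68 = 214.3 effective participants. The standard error is √[(0.24 × 0.76 + 0.365 × 0.635)/214.3] = 0.0440, and 0.125/0.0440 = 2.84. Power is 81.1% with the normal quantile and 78.9% with t on 34 degrees of freedom. The pooled formula used for the sample size gives 80.6% with the normal quantile.

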****Methods**:**

PARTY is a cluster randomised trial recruiting 42 general practices in Victoria, Australia. Baseline measures include: youth friendly practice characteristics; practice staff’s self-perceived competency in young people’s care and clinicians’ detection and response to risk taking behaviours and emotional distress in 14–24 year olds, attending the practice. Practices are then stratified by a social disadvantage index and billing methods and randomised. Intervention practices receive: nine hours of training and tools; feedback of their baseline data and two practice visits over six weeks. Comparison practices receive a three hour seminar in youth friendly practice only. Six weeks post-intervention, 30 consecutive young people are interviewed post-consultation from each practice and followed-up for self-reported risk taking behaviour and emotional distress three and 12 months post consultation.

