#### ***Recruiting and interviewing young people***

Young people were recruited into the trial in the ‘baseline profile’ and the ‘post-intervention’ phase (see Figure 2). The ‘baseline profile’ was collected prior to the randomisation of the practices to provide a snapshot of the young people seen by the clinician and to assess for baseline differences between the study arms after randomisation. The post-intervention sample of young people was a different sample from the baseline sample and became the study cohort followed up at 3 and 12 months.

a) Inclusion/exclusion criteria

All youth aged 14–24 years attending participating clinicians were eligible for participation. Exclusion criteria were: being physically or mentally (very) unwell (vomiting, febrile, weak, cognitively impaired or psychotic); unable to read or speak English; being under 18 years of age AND unable or unwilling to obtain parental consent AND judged by the clinician as incompetent to make an informed decision for participation in minimal risk research (that is, an immature minor) [61].

b) Recruitment and interview

Recruitment of young people into the study occurred in two phases. First, clinicians were trained to ask all eligible young people, after their consultation had finished, whether they would be willing for their contact phone number to be passed on to researchers for a full explanation of the study. GPs or PNs recorded telephone numbers of interested youth and any reasons for refusal or ineligibility; the clinicians were asked to fax this list to the researchers daily. The computer assisted telephone interview (CATI) staff telephoned all listed youth (usually on the same day) to fully explain the study and obtain formal consent. CATI staff then conducted the exit interview with consenting young people or made an appointment for the interview to take place at a time convenient for the young person. The interview (approximately 50 minutes long) could also be completed over several phone calls if not finished in one sitting. Young people were first notified by Short Messaging Service (SMS) to alert them that a call was coming from the project team. At the end of the interview, CATI staff obtained consent to telephone young people for the three month and 12 month follow-up periods. Follow-up interviews were approximately 20 minutes long. Young people had up to 20 telephone call attempts for up to two weeks before they were recorded as a missed recruit.

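### The two named prognostic covariates enter the model only if imbalanced, and each practice's pre-randomisation detection rate is left out, giving up some precision and letting the data pick the model

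*Protocol article*

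**What the plan says.** The Data analysis plan section specifies marginal regression by generalised estimating equations, with odds ratios for binary outcomes. Its covariates fall into two groups.

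- **Unconditional:** socio-economic status of the practice location, billing type, and recruitment method (clinician or research assistant).
- **Conditional as worded:** "imbalanced baseline factors identified a priori to be strongly associated with the outcome, namely the baseline risk factor status of young people", together with prior training in adolescent health. No rule says what counts as imbalanced.

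Detection is also measured at baseline. The Abstract (Methods) lists clinicians' "detection and response to risk taking behaviours and emotional distress" among the baseline measures. Table 1 gives both the recall-of-screening items and the clinician encounter form at baseline profile and post-intervention. The section on recruiting and interviewing young people places the baseline profile before randomisation and gives its purpose as a snapshot and "to assess for baseline differences between the study arms after randomisation". The profile is also fed back to intervention practices at the first practice visit. The same section states: "The post-intervention sample of young people was a different sample from the baseline sample".

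**The concern.** Adjustment gains precision through a covariate's association with the outcome, whether or not the arms happen to differ on it. The plan already calls these two factors strongly prognostic, then makes their entry depend on a balance check. Three things follow.

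1. When the arms look balanced, which is most of the time, the precision is discarded.
2. Each of two factors may be in or out, so up to 2 × 2 = 4 models are possible. The odds ratio is non-collapsible, so the quantity estimated changes with the covariates.
3. The practice's own earlier detection rate, a natural predictor of its later one, is not on the list although it is collected.

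The term baseline risk factor status is also ambiguous. The cohort and the baseline sample are different people, so it could be a practice-level value from before randomisation or the cohort member's own exit-interview report. These are different covariates.

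**Working it through.** **1. The plan's own figures (Sample size estimation).** Inputs: two-sided 5%, 80% power, "an intra-clinic correlation of 0.04", comparison-arm detection "equivalent to 24% of all presenting youth", and an intervention effect "equivalent to an additional 10% of all presenting youth to the practice", later revised to 12.5 points. With pooled variance, no continuity correction and VIF = 1 + (m − 1) × ICC:

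- Original, 24% v 34%: 323 per arm; VIF = 1 + 43 × 0.04 = 2.72; 2 × 323 × 2.72 = 1757 (stated 1760).
- Revised, 24% v 36.5%: 211 per arm; VIF = 1 + 17 × 0.04 = 1.68; 2 × 211 × 1.68 = 709, or 17.7 per practice, rounded up to 18 × 40 = 720 (as stated). Power at 720 is 80.6%.

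Both reproduce with no credit for baseline adjustment.

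**2. Gain from always adjusting for practice baseline detection.** Let m = 18 be the post-intervention number per practice, m0 the baseline number, and π the correlation of true practice rates between periods. The correlation of the observed practice means is

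r = π × ICC / √{[ICC + (1 − ICC)/m] × [ICC + (1 − ICC)/m0]}

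and the variance is multiplied by 1 − r². The article gives neither m0 nor π, so both are assumptions. Example at ICC 0.04, m0 = 10, π = 1: 0.04/√(0.0933 × 0.136) = 0.355, so 1 − r² = 0.874.

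| ICC | m0 | Variance removed, π = 0.5 to 1.0 |
|---|---|---|
| 0.01 | 10 | 0.4% to 1.4% |
| 0.01 | 18 | 0.6% to 2.4% |
| 0.04 | 5 | 1.8% to 7.4% |
| 0.04 | 10 | 3.2% to 12.6% |
| 0.04 | 18 | 4.6% to 18.4% |
| 0.07 | 10 | 6.2% to 24.7% |
| 0.07 | 18 | 8.3% to 33.1% |

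At ICC 0.04, power for the revised design rises from 80.6% to 81.9-85.6% (m0 = 10) or 82.4-87.9% (m0 = 18). These figures do not deduct the degree of freedom spent.

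The row m0 = 5 matters because the baseline window was two weeks. If baseline recruitment ran at the post-intervention average, taken as 30 youth in 86.3 days, a fortnight yields 14 × 30/86.3 = 4.9 youth per practice.

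**3. The adjust-if-imbalanced rule.** 20,000 simulated trials of 20 v 20 practice means, one practice-level covariate, imbalance taken as p < 0.05 (an assumption, since none is defined), and a true effect giving about 80% unadjusted power:

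| Covariate-outcome correlation | Power, never adjust | Power, adjust if imbalanced | Power, always adjust | Type I error, adjust if imbalanced |
|---|---|---|---|---|
| 0.3 | 81% | 81% | 83% | 4.8% |
| 0.5 | 80% | 81% | 89% | 4.0% |
| 0.7 | 80% | 82% | 97% | 3.6% |

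At a correlation of 0.2 all three strategies give about 80%. The simulation uses continuous practice means, not the planned logistic model, so it shows how the rule behaves rather than forecasting this trial's power. By step 2, baseline detection at ICC 0.04 reaches a correlation of at most 0.43 for m0 up to 18, so the 0.7 row does not describe that covariate.

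**The case against.** The strongest reply is that the article condenses a fuller plan, that an unseen analysis plan could add the detection covariate, and that the harm is lost efficiency only. Much of this stands.

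- **Omission.** The absence of baseline detection rests on reading the list after *namely* as closed, and a fuller plan could extend it. The imbalance condition, however, is written into the text and is not an omission.
- **Conditionality is limited.** Stratifiers and recruitment method enter regardless, and the conditional candidates are named in advance. A reader might infer open-ended covariate selection with an inflated false-positive rate; the text does not allow the first, and the simulation shows type I error below 5%.
- **A kinder reading.** The sentence may name two factors that will always enter. Then *imbalanced* does no work and should go.
- **The baseline data are used.** They serve description and practice feedback as well as the check between arms.
- **Which instrument.** The article does not say whether recall of screening or the clinician encounter form defines detection, so the same-measure argument must be put as whichever one does. Both are collected in both phases.
- **Hypothesis 2.** A reader might expect a smaller detectable difference from adjusting for exit-interview behaviour. No figure can be supported: the correlation is not given, the interview follows the consultation, and scaling a risk difference by √(1 − ρ²) is a linear-model shortcut.

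**Conclusion.** The point holds as a worthwhile improvement to the analysis, not as a flaw that threatens validity. The wording makes the entry of two prognostic factors depend on an undefined balance check, leaves one of them ambiguous, and does not use pre-randomisation detection in the model.

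The expected gain for hypothesis 1 is modest: about 3-18% of variance at the planning ICC of 0.04 (power about 82-88% against 80.6%), given 10-18 baseline youth per practice and a period correlation of 0.5-1.0. It is about 2-7% if the fortnight gave roughly 5 youth per practice, negligible at ICC 0.01, and larger at ICC 0.07.

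It would be tempting to conclude that the trial is underpowered or its sample size wrong. The documents do not support that: 1760 and 720 both reproduce without any baseline adjustment.

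**What to change.** 1. Delete *imbalanced*, so that the two named covariates always enter, alongside the stratifiers and recruitment method.
2. Add the practice's baseline-profile detection proportion to the hypothesis 1 model, taken from whichever instrument defines the detection outcome.
3. State that, for the 3- and 12-month behaviour outcomes, baseline risk factor status means the participant's exit-interview report of behaviour before the consultation. Do not adjust for exit-interview intention or readiness to change, which the consultation may already have altered.
4. Name this as the primary model and report unadjusted results alongside. Date the decision, because the Discussion says analysis is already underway.

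**Cost:** a change of wording and one extra practice-level covariate, about one degree of freedom among 40 practices. The data are already collected and no sample size changes.
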